## Abstract

**Background:**

Evidence has shown a relationship between dehydration, falls, and pulmonary aspiration among older adults in nursing homes, all of which contribute to loss of independence and quality of life. It is believed that improving communication among healthcare professionals in nursing homes (physicians, nurses, rehabilitation team, psychologist, social workers, dieticians and medical assistants) decreases the number of adverse events in institutionalized patients. This study will evaluate the feasibility of using a set of written signs, designed to caution against the risk of falls, dehydration, and pulmonary aspiration, and will enable the proposal of tailored interventions to manage these events in nursing homes.

**Methods/Design:**

All patients from Campus Neurológico Sénior (CNS) nursing home, at risk of falls and/ordysphagia and/or dehydration will be invited to participate in the study. Patients will undertake a screeningrisk assessment and the corresponding risk prompts will be attributed. Study duration will be a minimum ofthree months per participant, including daily record of falls, dehydration and pulmonary aspiration eventsand monthly interview assessments, conducted by a member of the research team. Data of the events that occur will be compared with historical data extracted retrospectively from medical and nursing charts. This study has been approved by the Ethics Committee of the Medical Academic Center of Lisbon, Faculty of Medicine, University of Lisbon (Ref. 176/15). All participants will give their written informed consent before entering the study.

**Discussion:**

This study is unique in evaluating the feasibility of a communication system in preventing the three major risks in nursing home. Thoughtful selection and display of proper risk prompts in nursing homes could be an essential step along a path toward efficient communication of risks among healthcare teams. We expect that the displays will be easily applicable given their simplicity, low complexity, and minimal physical requirements.

**Trial registration:**

NCT03123601. March 7, 2017. Retrospectively registered.

## Background

Due to demographic ageing and increased life expectancy, an increasing number of elderly spend the end of their life in an institutional setting [1].

Nursing homes provide 24-h nursing care to residents with heterogeneous diagnoses, different degrees of functional status, and complex care needs [2]. Falls, pulmonary aspiration, and dehydration are a particular problem in nursing homes and a major contribution to the deterioration of independence and quality of life of residents [2–7].

The incidence of falls and fall-related injuries, which is a major external cause of death in those living in healthcare institutions, has been reported in numerous epidemiologic studies [8–10]. Choking and aspiration pneumonia are also frequent; choking is the most common external cause of death in residents under 65 years old, while aspiration pneumonia is particularly difficult to diagnose since the moment of aspiration is usually not observed [8–11]. Dehydration, due to poor fluid intake or pathologic loss of body fluids, is considered to be present in 0.8 to 1.4% of nursing home residents. It is associated with frailty, poor cognition, falls, delirium, disability, and mortality and is a major cause of decreased attention and fluctuating mental status, the hallmarks of delirium, in the nursing home [12].

To provide high-quality care and prevent these risks, nursing home multidisciplinary team members (i.e., physicians, nurses, professionals from rehabilitation team, psychologists, social workers, and medical assistants) need to work as a coordinated team, have an effective system of communication with access to information, and understand the residents’ needs [13, 14].

The use of risk prompt displays by nursing home patients may improve the access to information and communication between healthcare professionals, which may in turn reduce the number of falls, dehydration, and pulmonary aspiration events. As soon as a patient is admitted, the nursing team would be responsible for screening for falls, dehydration and pulmonary aspiration risks, and for suggesting the corresponding risk prompt displays that should be used. The local multidisciplinary team would validate the nursing team’s suggestions before a patient would start using the risk displays in their daily routine in the nursing home.

The aim of this study is to develop and evaluate the feasibility of a set of risk prompt displays to communicate the risk of falls, dehydration, and pulmonary aspiration and to reflect on tailored interventions that would appropriately manage these events in nursing homes. In order to do this, a national, single-center, feasibility study will be conducted. The duration of the study for each participant will be a minimum of 3 months.

## Methods

### Study setting

Participants will be recruited from Campus Neurológico Sénior (CNS), a neurological nursing home, located in Torres Vedras, Portugal, which has an outpatient clinic and a residential unit for short or long-term admissions of neurologic patients or individuals aged over 65 years. CNS places its focus on comprehensive care to patients, implemented by a multidisciplinary healthcare team that includes physicians, nurses, a rehabilitation team, dieticians, psychologists, and medical assistants.

### Eligibility criteria

All patients from the CNS residential unit (*n* = 78) who fulfil the following inclusion criteria will be invited to participate:Men or women residing at the CNS nursing home for long-term care;Risk of falling and/or dysphagia and/or dehydration defined by brief screening assessment;Willing to participate in the study;Willing to provide written informed consent;Willing to comply with the monthly required interviews.

Exclusion criteria include the presence of significant active psychiatric problems (e.g., hallucinations, confusion, psychosis) that, according to the clinical judgement of the CNS multidisciplinary team, could be aggravated with the use of risk reminders.

### Recruitment and intervention

#### Study materials (Figs. 1 and 2)

Created by the CNS risk prompt display study group, the risk reminders are intended to be used by residents, from the moment of admission, in daily routines at the CNS (following validation with the present feasibility study). They include the following standardized materials:Small, lightweight rubber coloured bracelets, for patients’ use (on the wrist, visible), with phrases related to the different risks: “prevent rather than fall”, “contain to protect”, “drink to hydrate”, and “avoid choking”.Small and coloured signposts next to the patients’ headboard.

**Fig. 1 Fig1:**
[figure not shown]
Risk prompt displays—coloured bracelets with slogans related with the different risks

**Fig. 2 Fig2:**
[figure not shown]
Risk prompt displays—coloured signposts next to patients’ headboard

### Procedures

#### Preparation phase—teaching session for healthcare professionals

One member of the research team will hold an initial multidisciplinary teaching session to train and familiarize the CNS multidisciplinary team with the use of sign displays and the corresponding intervention procedures. Training is expected to last 60 min and to be both a theoretical and practical session. It will include explanations of what constitutes a fall, pulmonary aspiration, and dehydration, and will also include specific instructions on which procedures to undertake at each situation of risk. Additionally, the researcher will provide a practical demonstration of the procedure and any queries from the team will be answered.

#### Screening

All patients will be invited to participate if they fulfil the aforementioned inclusion criteria. The nursing team from the CNS will propose patients for recruitment. Patient risk assessment and inclusion in the study will require clinical assessment and a history taking, before validation by the CNS multidisciplinary team.

For the purpose of participant recruitment, a fall is defined as a sudden, unexpected event that results in coming to rest unintentionally on the ground or at some other lower level [15, 16]. A near fall is defined as an involuntary or uncontrolled descent not ending on the ground or at some other lower level [17]. Given our interest in the phenomena and not the cause, all falls, either resulting from environmental hazards or overwhelming external force, disease-related symptoms, and/or attributable to acute medical events such as syncope and seizures, will be considered.

A dysphagia or pulmonary aspiration event will be defined as inefficient or unsafe transfer of food, liquid, or saliva from the mouth into the stomach [18].

Dehydration will be defined by the loss of body water, with or without salt, at a rate greater than the body can replace it [19].

At the end of screening and risk assessment, the corresponding risk messages will be given to the patient by the investigator.

If patients are unable to give informed consent, legal guardians will be asked for consent and authorization of a screening visit. Informed consent containing comprehensive information about objectives, duration, procedures, willingness, and possible risks to study participation, will be obtained from patients before any study-related proceedings. Patients will be encouraged to take time to think and clarify any doubts they may have before signing informed consent and, when they feel ready, to communicate the decision to one of the members of the research team. During the screening visit, an explanation of the objectives and compliance needed for the study will be given to the participants and caregivers and all questions will be considered and answered.

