#### Diary records

At the end of each nursing shift all events—falls, near falls, dehydration, and pulmonary aspiration—will be recorded in documents specifically created for this purpose, by the CNS risk prompt display study group.

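### The only definition shown for a pulmonary aspiration event describes impaired swallowing, which is close to an entry criterion, and the dehydration definition names no countable event

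*Protocol article*

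**What the plan says.** All references are to the protocol article.

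- **Screening, aspiration.** One definition covers two conditions: "A dysphagia or pulmonary aspiration event will be defined as inefficient or unsafe transfer of food, liquid, or saliva" from mouth to stomach.
- **Screening, dehydration.** "Dehydration will be defined by the loss of body water, with or without salt, at a rate greater than the body can replace it".
- **Screening, falls.** The definitions open with a recruitment qualifier: "For the purpose of participant recruitment, a fall is defined as a sudden, unexpected event". Grammatically it is attached to the fall sentence only.
- **Eligibility criteria.** Entry requires "Risk of falling and/or dysphagia and/or dehydration defined by brief screening assessment".
- **Diary records.** "At the end of each nursing shift all events—falls, near falls, dehydration, and pulmonary aspiration—will be recorded" on forms made for the study.
- **Preparation phase and Monthly visits.** Staff are taught what counts as each event, and the event definitions are repeated every month. No second set of definitions appears in the article.
- **Secondary outcomes and Statistical analysis.** The number of aspiration and dehydration events is a secondary outcome, expressed relative to days of hospitalization and compared with the same period one year earlier.
- **Source of the comparison.** Data collection of events and Statistical analysis both take medical and nursing charts for the two periods. The Abstract can be read as events recorded during the study against historical chart data.

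**The concern.** An outcome event should be something that happens, can be dated and can be counted. The fall definition has that form. The other two do not.

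The aspiration wording describes how a swallow performs and does not require material to reach the airway. A resident who entered because of dysphagia can satisfy it through the same trait that made them eligible. The Background adds a practical difficulty: "aspiration pneumonia is particularly difficult to diagnose since the moment of aspiration is usually not observed". What staff can see is the swallowing difficulty, and that already meets the definition.

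The dehydration wording describes an ongoing imbalance. It gives no sign, threshold, start or end, so it does not say when one event has occurred or when a second one begins.

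At stake is whether the event rates for two of the three conditions can be read as adverse events that the prompts might prevent, or whether they partly reflect how many residents have a standing condition. The Discussion says the results will inform later trials and their outcomes, so an unclear event rate would carry forward.

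**Working it through.** The article states no event rate, and its sample size of 20 is a pragmatic choice without alpha, power or effect size. There is no figure to reproduce. The check is a comparison of texts, followed by an illustration of how much the counting rule matters.

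**Step 1: entry state against outcome event.**

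| Condition | Entry criterion | Definition shown | Discrete event? |
|---|---|---|---|
| Falls | Risk of falling | Sudden, unexpected event ending on the ground or a lower level | Yes |
| Aspiration | Risk of dysphagia | Inefficient or unsafe swallowing | No; airway entry not required |
| Dehydration | Risk of dehydration | Water loss outpacing replacement | No; no onset, end or threshold |

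In the aspiration row the entry criterion and the outcome definition concern the same trait. The fall row shows that a discrete definition was within reach.

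**Step 2: do the definitions reach the outcome data?** The qualifier points to recruitment. However, the aspiration sentence defines an event, whereas recruitment rests on risk found by a brief screen. Staff are also trained on and reminded of event definitions, and these are the only ones shown. It is reasonable to take them as those used in follow-up, though the article does not say so outright.

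**Step 3: the year-on-year comparison.** In the Methods, both years come from charts. The source is the same, but study-period charts are written by staff trained on these definitions and reminded of them. Nothing indicates that the prior-year charts followed them. What is charted as an event may therefore change between periods, apart from any effect of the prompts.

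**Step 4: sensitivity to the counting rule (illustration).**

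Inputs: 20 patients (Statistical analysis); minimum follow-up of 3 months, taken as 90 days; 2 to 3 shifts a day (assumption, not in the article).

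- Patient-days: 20 × 90 = 1,800.
- Records from one persisting case if logged every shift: 2 × 90 = 180 to 3 × 90 = 270.
- Rate with one such case: 1000 × 180 / 1,800 = 100 to 1000 × 270 / 1,800 = 150 per 1,000 patient-days.
- Rate if it is counted once: 1000 × 1 / 1,800 = 0.56 per 1,000 patient-days.
- With four such cases: 4 × 100 = 400 to 4 × 150 = 600 if logged every shift, against 1000 × 4 / 1,800 = 2.22 if each is counted once.

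This shows how far the rate depends on a rule the article does not give. It does not predict what staff will do.

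**The case against.** The defence has several good points.

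- **Counting.** A reader might infer that a chronic state will be counted at every shift. The article does not say that. The Diary records section fixes when forms are completed, and an episode rule could sit in those forms or in the full protocol, neither of which is shown. The same applies to a dehydration threshold. This stands: the missing rule is not itself the error.
- **Comparability.** A reader might also infer that study counts cannot match the prior-year charts because shift records are set against them. Data collection of events and Statistical analysis plan charts against charts. Only the Abstract suggests otherwise. This stands; what remains is possible drift in charting and an inconsistency to resolve.
- **Risk is not disease.** Residents enter on risk of dysphagia, so not every swallow of every such resident is impaired, and unsafe transfer can include entry into the airway. This is true, but the definition is met without airway entry, which is the point.
- **Observability.** The GULP tool uses fluid intake, urine colour and clinical risk factors, which nurses can observe. It would be wrong to say dehydration cannot be assessed on the ward. However, GULP is listed for the baseline risk assessment and is not tied to the event definition.
- **Context.** The definitions sit under Screening, the outcome is secondary and descriptive, and the Discussion admits that training and monthly reports may raise registration. That admission concerns how many events are registered. Its remedy, widening collection to all residents and to the year before, does not settle what counts as an event.

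**Conclusion.** The point holds in a limited form. The published wording for an aspiration event is a definition of impaired swallowing, so an eligible resident can meet it with no aspiration. This is a wrongly stated rule and not merely an omitted detail: a fuller document would have to depart from the wording to cure it. The dehydration wording names a process where the analysis needs a count; the threshold and episode rule may exist elsewhere.

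The effect on the results cannot be computed from the article. Under the assumed 2 to 3 shifts and 90 days, the choice between logging every shift and counting episodes changes one persisting case from 1 to between 180 and 270 records. The documents do not establish which will apply.

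The conclusion assumes that the definitions shown are those used in training and reminders. It concerns a secondary, descriptive outcome. The primary outcome, adherence to the prompts, and the sample size of 20 are unaffected. Correction is advisable for the sake of interpretation, but the feasibility question does not depend on it.

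**What to change.** 1. Keep dysphagia and dehydration risk, as assessed by SDQ and GULP, as eligibility states only.
2. Define the two secondary outcomes separately, as new episodes identifiable in the chart: a choking or aspiration episode, including recorded aspiration pneumonia; and a clinician-recorded dehydration episode. Count each once per episode, and state when a further record is a new episode.
3. Apply the same written abstraction criteria to the charts of both periods.
4. Reconcile the Abstract with Data collection of events and Statistical analysis, so that shift diaries are not compared with historical charts.

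The cost is the rewording of two definitions, an abstraction form and one sentence in the Abstract. The downside is that unwitnessed aspiration and mild dehydration go uncounted. That loss need not be equal in the two periods, because trained and reminded staff may chart more, so this limitation should be reported with the comparison.

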#### Baseline assessment

Demographic data, clinical manifestations and disease management, comorbidities, and past medical conditions will be obtained using a structured questionnaire. In addition, a brief clinical assessment of risk of falls, pulmonary aspiration, and dehydration, including the clinical scales listed below, will be performed.

### Mini Mental State Examination (MMSE) [20]

The MMSE is a brief 30-item questionnaire that is used to quantitatively assess cognition. The MMSE test consists of 11 simple questions grouped into 7 cognitive domains: the time and place of the test, repetition of three words, attention and calculation, recall of three words, language use, and visual construction. It can be used to screen for cognitive impairment (cut-off scores: none: 24–30; mild: 18–24; and severe: 0–17), to estimate the severity of cognitive impairment at a given point in time, to follow the course of cognitive changes over time, and to document an individual’s response to treatment.

### Timed Up and Go Test (TUG) [21–23]

The TUG is a quick capacity measure to assess frailty, functional mobility and is a good predictor of an individual’s ability to independently walk outside safely. It requires that the participant get up from a standard chair, walk 3 m at a comfortable and safe speed and then turn walk to back to sit in the chair. The TUG is recommended in the latest physiotherapy guidelines and by the International Parkinson and Movement Disorder Society (MDS) Rating Scales Committee as an instrument to assess posture, gait, and balance in Parkinson’s disease. It is also recommended as a tool to identify frailty and risk of fall in the older population (cut-off score indicating risk of falls > 13.5 s).

### Morse Fall Scale [24]

The Morse Fall Scale assesses the risk of falling for hospital inpatients or those in long-term care. In particular, it evaluates fall history, the presence of comorbidities, the use of walking aids, mental status, and whether or not patients are receiving intravenous therapy. Each criterion evaluated receives a score ranging from zero to 30 points, summed to provide a risk score, which is classified as follows: low risk, from 0 to 24; mean risk, 25–44; and high risk, ≥ 45.

### Swallowing Disturbance Questionnaire (SDQ) [25, 26]

The SDQ for Parkinson’s disease patients is a validated self-reporting 15-item questionnaire on swallowing disturbances that appear in the oral and pharyngeal phases of swallowing. Fourteen questions rated on a four-point scale (0 for no disturbance and 3 for severe disturbance) and one dichotomous question (“yes/no”; yes is scored 2.5 and no is scored 0.5). If the patient is unable to respond, a CNS nurse familiar with the patient’s history will complete this questionnaire.

### GULP dehydration risk screening tool [27]

The GULP is a screening tool to assess geriatric dehydration risk. It includes a score from 0 to 7 points for three categories (24 h fluid intake; urine colour; clinical risk factors for dehydration). Based on results, the GULP tool recommends a hydration management plan, thereby engaging the patient in self-monitoring of urine and verbal prompts.

#### Diary records

At the end of each nursing shift all events—falls, near falls, dehydration, and pulmonary aspiration—will be recorded in documents specifically created for this purpose, by the CNS risk prompt display study group.

#### Monthly visits

At the end of each month, patients will undergo an interview performed by a nurse (member of the research team), and a self-completed questionnaire will be handed to healthcare professionals. Both will be questioned regarding overall acceptability levels and asked about any problems encountered regarding the use of the risk prompts. Additionally, these moments will include questions on clarity of the instructions, a reminder of the event definitions and the registration procedures.

In order to avoid excluding demented patients, if the patient is unable to answer the questions, only the occurrence of adverse events and the reason for not performing the interview will be recorded.

#### Monthly reports

At the end of each month, as a strategy to keep healthcare professionals informed and to ensure they remember the importance of registering events, a newsletter will be sent to all CNS staff. This will contain information about the study duration and will present a summary of the number of participants in the study (number of patients recruited and number of drop-outs) and of the falls, dehydration, and pulmonary aspiration events recorded in that month.

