#### Secondary outcomes

The secondary outcomes will be to evaluate the following:Patients’ and health professionals’ satisfaction;The efficacy of risk prompt displays in reducing the number of falls, pulmonary aspiration, and dehydration events;The type and frequency of adverse events that arise from using the risk prompt displays (for example, physical or social discomfort, skin irritability, stress, or anxiety).

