### Statistical analysis

Statistical analysis will be performed using SPSS® version 21.0; SPSS Inc. Chicago, IL [28]. Data will be described using descriptive statistics, i.e., means, medians and relative frequencies (i.e., outcome per number of days of hospitalization).

As this is an exploratory study with no previous studies having been conducted, we defined 20 patients as enough to conclude on the primary outcome on feasibility. This is a compromise between the capability to respond to a specific question and a realistic perspective of recruitment capacity using just one nursing home [29].

As our primary outcome, we will measure patients’ adherence to the risk prompts through the number of times and reasons they remove the risk prompts or refuse to use prompts during the period of the study and/or withdrawing from the study.

The secondary outcomes will be the following:Patients’ satisfaction with the risk prompt displays measured on a 7-point Likert scale and open-ended questions.Healthcare professionals’ satisfaction with the risk prompt displays as measured on a 7-point Likert scale and open-ended questions regarding the overall benefits of using the displays and overall perception of its impact on decreasing risk.Historical comparison of medical and nursing charts data on the relative frequency of number of events per number of days of hospitalization registered during the period of the study, with the same period the year before.Type and frequency of adverse events recorded during the period of the study.

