## Discussion

Thoughtful selection of proper risk prompt displays in nursing homes is an essential step along a path toward efficient communication of risks among teams. We expect that the displays will potentially improve communication given their simplicity, discretion, low complexity, and minimal physical requirements.

The results of the study will enable the planning, at a later stage, of clinical studies designed to respond to more pragmatic questions regarding the use of risk prompt displays, such as (1) efficacy of the use of the risk prompt displays, (2) better clinical trial design to evaluate the efficacy of displays, including outcomes, (3) a better treatment strategy including the combination of non-pharmacological therapies with the use of the risk prompt displays, and 4) introduction of the use of a risk prompt bracelet in the therapeutic areas studied.

A limitation of this study is that the teaching session or the monthly reports encourage event registration, resulting in an apparent increase of events during the period of the study. For that reason, we will widen data collection to all CNS residents, and will also collect data of events in the same period, 1 year before.

This study will only be conducted in one nursing home, which could be a limitation. However, the CNS population is representative in age, heterogeneity of diagnosis, and symptoms of other nursing homes. As this is a protocol for a first exploratory study, we anticipate that running the study in just one nursing home will not compromise the capability to conclude on patients’ adherence.

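### The secondary outcome is worded as efficacy of the displays, but the year-on-year comparison estimates the change after a package of training, reminders, newsletter and prompts, mixed with any change in recording

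*Protocol article*

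**What the plan says.** All places are in the protocol article.

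- **Outcome.** Secondary outcomes lists "The efficacy of risk prompt displays in reducing the number of falls, pulmonary aspiration, and dehydration events".
- **Estimate.** Statistical analysis describes a historical comparison of chart data: events per day of stay "registered during the period of the study, with the same period the year before". Data collection of events says that charts are the source in both periods and that all residents are covered. No other comparison is stated for this outcome.
- **Teaching session.** Before the study period, a member of the research team will "hold an initial multidisciplinary teaching session to train and familiarize the CNS multidisciplinary team" in the use of the signs. The content includes event definitions and "specific instructions on which procedures to undertake at each situation of risk".
- **Monthly reminders.** The Monthly visits section adds "a reminder of the event definitions and the registration procedures".
- **Newsletter.** Under Monthly reports, "a newsletter will be sent to all CNS staff" each month. Besides recruitment and drop-out figures, it carries a summary "of the falls, dehydration, and pulmonary aspiration events recorded in that month".
- **Acknowledged limitation.** The Discussion says that "the teaching session or the monthly reports encourage event registration, resulting in an apparent increase of events during the period of the study". Its answer is to collect events for all residents and for the same period one year before.

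**The concern.** The prompts, the training, the reminders and the newsletter all start with the study. Nothing in the article places any of them in the comparison year, and a newsletter reporting study recruitment could not have existed then. A difference between the two years therefore carries all of them at once.

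The protocol recognises one consequence, more registration, which pushes the observed rate up. It does not recognise the other. Instruction on what to do when a risk is present, and monthly feedback of event numbers, may change care and reduce true events. That pushes the rate down, in the direction that would be read as benefit from the bracelets and signposts.

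What is at stake is the reading of this outcome when later trials are planned, which the Discussion gives as the purpose of the results. A fall in events could be credited to the displays when staff training caused it, or a real benefit could be hidden by better recording.

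**Working it through.** The article states no event rate, effect size or power for this outcome, so there is no figure to reproduce. The check is about which effects the stated comparison can tell apart.

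**Inputs from the article:** 20 planned participants (Statistical analysis); 78 residents in the unit (Eligibility criteria).

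**Assumed inputs, for illustration only:** rate ratio of the displays *p* = 0.7, 0.8 or 1.0; rate ratio of training plus feedback *c* = 0.7 to 1.0; recording ratio, study year over prior year, *a* = 1.0 or 1.25.

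**Step 1. Before-after ratio in prompt users.** Observed RR = *p* × *c* × *a*.

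Displays inert (*p* = 1):
- *a* = 1.0: 1 × 0.7 × 1.0 = 0.70; 1 × 0.9 × 1.0 = 0.90.
- *a* = 1.25: 1 × 0.7 × 1.25 = 0.875; 1 × 0.9 × 1.25 = 1.125.

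Three different situations give the same observed 0.80:
- A, displays only: 0.8 × 1.0 × 1.0 = 0.80.
- B, training and feedback only: 1.0 × 0.8 × 1.0 = 0.80.
- C, both, with 25% more recording: 0.8 × 0.8 × 1.25 = 0.80.

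**Step 2. Does the Discussion's remedy help?** Take the all-resident total, with share *s* = 20/78 = 0.256 using prompts (assuming that the planned number is also the number enrolled), equal baseline rates and unchanged recording: RR = *c* × [*s* × *p* + (1 − *s*)].
- Displays at 0.7, training and feedback inert: 0.256 × 0.7 + 0.744 = 0.923.
- Displays inert, training and feedback at 0.8: 0.8 × 1 = 0.80.

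The total dilutes a display effect and passes a staff-level effect through in full. A change in recording multiplies the total by *a* in the same way. All-resident and prior-year totals therefore remove neither bias.

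**Step 3. Can the same data be used better?** Non-participants share *c* and *a* but have no prompts, so their before-after ratio is *c* × *a*. Dividing the participants' ratio by it gives (*p* × *c* × *a*)/(*c* × *a*) = *p*, if the shared effects are equal in both groups and nothing spills over.
- A: 0.80/1.00 = 0.80.
- B: 0.80/0.80 = 1.00.
- C: 0.80/1.00 = 0.80.

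Under those assumptions the contrast separates B from A and C. The data for it are already to be collected, but the article does not state the contrast.

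**The case against.** Several points on the other side stand.

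- **Part of the training delivers the prompts.** A bracelet works only through staff who know what it means and what to do. A reader might infer that the whole session is a foreign co-intervention; the article does not support that, since it describes the session as familiarising staff with the signs and the procedures that go with them. But if training belongs to the intervention, the estimate is of a package, and the outcome should say so. The reminders and newsletter remain extra in either case.
- **The analysis is modest.** The study is called exploratory, the analysis is descriptive, no hypothesis test is stated for this comparison, and the Discussion leaves efficacy to later studies. This limits the weight of the point. It also makes the efficacy wording in Secondary outcomes out of step with the rest of the article.
- **The limitation is partly acknowledged.** The Discussion already names the session and the reports as distorting the comparison, but in one direction only, and its remedy does not remove that distortion.

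Three stronger readings are tempting and not supported. One is that the effects cannot be separated at all: the all-resident data permit the partial contrast in Step 3. Another is that the new shift record itself creates the difference: the stated comparison uses charts in both years, so only an indirect effect on charting is plausible. The last is that event counts must come out of the newsletter: staff already see who wears prompts, the newsletter is meant to encourage registration, and removing the counts would leave the training, the reminders and the historical design in place.

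**Conclusion.** The concern holds as a mismatch between the outcome's wording and its estimator. The stated comparison measures the change in charted event rates after a package was introduced, combined with any change in recording. It does not measure the efficacy of the displays alone. The two unaddressed influences have opposite signs, so neither a favourable nor a null result can be read as evidence about the displays.

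No size can be given from the documents. The ratios above follow from assumed inputs and show only that inert displays can produce ratios on either side of 1. The conclusion rests on two readings of the article: that training, reminders and newsletter were absent in the comparison year, and that they reach staff across the facility. The primary outcome, adherence to the prompts, is not affected.

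**What to change.** 1. **Secondary outcomes and Statistical analysis:** reword the item as an exploratory before-after change in event rates following introduction of the package (training, reminders, newsletter, prompts). State that it does not estimate the efficacy of the displays alone.
2. **Discussion:** add a true reduction in events from training and feedback as a second bias, opposite in direction to increased registration. State that all-resident and prior-year totals remove neither.
3. **Statistical analysis:** describe the change in participants beside the change in non-participants, using the chart data already planned. Present it as a partial check, limited by selection on risk and consent and by spill-over to residents without prompts.

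The cost is a narrower claim and slightly more descriptive analysis; no new patients or data sources are needed. Leaving event counts out of the newsletter is optional and not part of this fix.
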